#### Missing data

Missing data introduce uncertainty about unobserved values and their potential influence on parameter estimates and study conclusions [16, 17]. Application of recent developments in non-ignorable data (i.e., missing not at random) will include pattern mixture models, semiparametric models (e.g., inverse probability weighted), and stratification-based analyses [18, 19]. Sensitivity analyses will determine the extent to which conclusions depend on the assumptions about unobserved values [20]. Identification of missing data patterns will ensure that relevant covariates are included implicitly (i.e., auxiliary variables) or explicitly, as appropriate. Based on our previous research with Latino MSM, we do not expect attrition or missing data to be a significant issue; however, we are well prepared in the event that it occurs.

#### Power analysis

The sample size of 150 male couples (*n* = 300) was chosen to ensure sufficient power to detect differences in the proportion of HIV-protected sex acts between treatment conditions with a significance level of α = 0.05. Autocorrelation was estimated to be 0.15 and intraclass correlation was estimated to be 0.66; these estimates were derived from prior MSM couple-based intervention research studies for conjoint, condom-use variables [21]. We assumed a pre-intervention proportion of HIV-protected acts of 30%, based on pilot study data collected from Latino men in same-sex relationships. Power analyses also utilized an effect size involving a 12 percentage point increase in HIV-protected acts (i.e., a small-to-moderate effect size). Results indicate that 80% power is achieved for our primary outcome with a final sample size of 63 couples/arm; this extrapolates to a starting sample of 75 couples/arm (or a total of 150 couples) if we model the final sample size to include 15% attrition. Prior couple-based research found significant differences for behavioral outcomes with as few as 60 couples/arm [22, 23]. Actual power is likely to be higher due to (1) gains in efficiency via covariance adjustment, (2) analysis will use data provided by participants prior to their attrition (whereas power analyses assumed all data from an attrited participant would be unavailable), and (3) the likelihood of > 85% retention, based on the team’s successful retention in previous research with Latino male couples.

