### Data analysis

Initial data analysis tasks will involve univariate and bivariate statistics to characterize the sample and review the distributional properties of measures across treatment arms. To evaluate the efficacy of the intervention, we will use random effect models and/or generalized estimating equations (GEE) modeling 6-month follow-up differences, adjusting for characteristics at baseline, 3-months, and treatment arm in order to increase statistical precision. GEE models will consistently be used in cases where unobserved heterogeneity invalidates the application of random effect models. Additional covariates will be included as indicated by comparison of baseline differences and variables of theoretical importance (e.g., serostatus concordance). We will also explicitly test baseline × treatment interactions. We expect to model our main outcome as a continuous variable, but based upon examination of pilot data, some adjustment for interval censoring (i.e., considerable proportions reporting condom use on all or no occasions) may be required in order to meet distributional assumptions.

Following evaluation of Aim 2, we will perform a set of exploratory analyses to develop dyadic models for sero-discordant couples in which partners are not exchangeable in terms of risk [15]. We will also explore factors associated with the magnitude of treatment effects (i.e., potential moderators) as well as potential mediators. Effect modification will be evaluated directly through random effects models or as multiplicative composites in GEE models. Hypothesis testing will implement an intention-to-treat approach. We will employ GEE to account for the non-independence in measures arising from (1) “autocorrelation”, due to repeated measures with the same person, and (2) “intraclass correlation”, arising from partners in a dyad who are reporting on behaviors conjoint within that dyad.

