### Limitations

Despite its unique advantages, there are several limitations. We will recruit a convenience sample, which limits generalizability. We acknowledge that the sample may not reflect the general population of Latino MSM. The budgetary constraints and the length of the project period of the MARI initiative limit our ability to include a 12-month follow-up. Thus, while we may detect change at 3 or 6 months post intervention, we will not be able to determine if the effects are sustained over time. Our sample size, although adequate to test for intervention effects, is not powered for efficacy. Thus, we cannot test the effects of moderators or mediators; moderation and mediation analysis are exploratory. Our primary outcome is limited to sexual activity with main partners. While appropriate for testing a couple-based intervention, we recognize that the HIV risk and protection with outside partners should also be considered. We will be conducting these as secondary analysis.

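### The stated 80% power with 63 couples per arm is not reproduced by the printed inputs for the 6-month contrast; it needs a small, unstated SD or a two-visit contrast

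*Protocol article*

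**What the plan says.** The Power analysis section sets the test "with a significance level of α = 0.05" and does not say whether it is one- or two-sided. On clustering it says: "Autocorrelation was estimated to be 0.15 and intraclass correlation was estimated to be 0.66". The starting proportion is 30% and the effect is "a 12 percentage point increase in HIV-protected acts (i.e., a small-to-moderate effect size"). From these it concludes: "Results indicate that 80% power is achieved for our primary outcome with a final sample size of 63 couples/arm". Allowing for 15% attrition, this becomes 75 couples per arm. The section adds that actual power is probably higher, for three reasons: covariate adjustment, use of data collected before dropout, and better retention than assumed.

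The Data analysis section describes the efficacy analysis as "modeling 6-month follow-up differences", adjusted for baseline and 3-month characteristics. It also says that GEE will handle repeated measures on the same person. The outcome is expected to be continuous, with a possible adjustment because of "considerable proportions reporting condom use on all or no occasions".

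The Limitations section says: "Our sample size, although adequate to test for intervention effects, is not powered for efficacy". The sentence after it concerns moderators and mediators.

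**The concern.** A correlation of 0.66 between partners removes much of the information in the second partner's report. A difference of 30% against 42% is modest, and 63 couples looks few for it at a single visit. The power statement gives neither the SD of the outcome nor the number of follow-up visits used. The section that names the contrast points to 6 months, while the autocorrelation input points to more than one visit.

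What is at stake is how a null result is read. If readers accept 80% power for 12 points, a non-significant 6-month result will count as evidence against an effect of that size. If the true power is nearer one third or one half, such a result is about as likely as not, or more likely than not, even when the effect is real.

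**Working it through.** **Inputs.** From Power analysis: 63 couples (126 men) per arm, proportions 0.30 and 0.42, α = 0.05, intraclass correlation 0.66, autocorrelation 0.15. From Data analysis: the 6-month contrast and a continuous outcome. Assumed here: a two-sided test and the SD, which is varied.

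**1. Attrition step.** 63/0.85 = 74.1, so 75 per arm covers it. This step is sound; the question is the 63.

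**2. Trying to reproduce 80%.** At binomial variance, 30% against 42% needs (1.960·√(2·0.36·0.64) + 0.842·√(0.30·0.70 + 0.42·0.58))²/0.12² = 250 independent observations per arm. No two-sided calculation that was tried with both stated correlations at binomial variance reaches 80%.

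**3. Effective size.**
- 6 months only: 126/(1 + 0.66) = 75.9 per arm.
- Average of 3 and 6 months: 252/(1.66 × 1.15) = 132.0 per arm.

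**4. Power at binomial variance, two-sided.**
- 6 months: Φ[(0.12 − 1.960·√(0.4608/75.9))/√(0.4536/75.9)] = 0.34.
- Two visits: the same formula with 132.0 gives 0.53.
- One-sided, the figures are 0.46 and 0.65.
- 80% at 6 months would need about 250 × 1.66/2 = 207.5, or 208 couples per arm.
- The approximate detectable difference at 80% is 2.802·√(0.4536/75.9) = 21.7 points at 6 months and 2.802·√(0.4536/132.0) = 16.4 points for two visits.

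**5. Power on a continuous scale, two-sided.** Power = Φ[0.12/(SD·√(2/n)) − 1.960].

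| Assumed SD | 6 months (n = 75.9) | Two visits averaged (n = 132.0) |
|---|---|---|
| 0.264 | 80% | 96% |
| 0.289 (uniform on 0 to 1) | 72% | 92% |
| 0.30 | 69% | 90% |
| 0.35 | 56% | 80% (0.795) |
| 0.40 | 46% | 68% |
| 0.45 | 38% | 58% |
| 0.48 | 34% | 53% |

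Solving for 80%: SD = 0.12/(2.802·√(2/n)), which is 0.264 at 6 months and 0.348 for two visits. One-sided, the limits are 0.297 and 0.392.

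**6. Is an SD of 0.264 plausible?** It is tighter than a uniform spread (0.289). The plan expects many men at all or none, which widens the spread. As an illustration with mean 0.30, put 40% at 0, 10% at 1, and the rest at mean 0.40 with variance 0.06. The variance is 0.10 + 0.50·(0.06 + 0.16) − 0.09 = 0.12, so the SD is 0.346. Milder heaping, with 35% at 0, 5% at 1 and a middle variance of 0.05, gives 0.307. At these SDs the 6-month power is 57% and 67%; the two-visit power is 80% and 89%.

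**7. Grounds for higher power.** If 0.15 is also the correlation between baseline and follow-up, adjusting for the baseline outcome leaves 1 − 0.15² = 0.9775 of the variance, a gain of about 2%. With no attrition at all, n at 6 months is 150/1.66 = 90.4. That gives 39% at binomial variance, and 80% needs an SD of 0.12/(2.802·√(2/90.4)) = 0.288 or less.

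**The case against.** The strongest reply is that power for a mean proportion depends on its SD and the article gives none. Binomial variance is close to the worst case for an outcome the plan expects to treat as continuous. An autocorrelation is listed, and GEE for repeated measures is described, so the authors may have powered a two-visit analysis. With an SD of about 0.348 that analysis has 80% power using both stated correlations. The standardised effect is then 0.12/0.348 = 0.345, which fits the small-to-moderate label. All of this stands, and it is why 80% is unsupported for the named contrast rather than shown to be wrong under every reading.

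Three stronger inferences should be resisted.
- A reader might infer that the plan's own inputs fix the 6-month power below one half. They do not: the figure moves with the SD, and step 6 shows heaped distributions with power above that.
- A reader might notice that 63 × 2 partners × 2 visits = 252, close to the 250 independent observations needed, and infer that the correlations were ignored. That is a numerical match (252 independent reports give 80.3%); the document does not show how 63 was obtained.
- A reader might take the Limitations sentence as a flat denial of the power claim. The same sentence calls the sample adequate to test intervention effects, the next one turns to moderators and mediators, and the article describes its goal as preliminary efficacy. The wording is unclear, not a plain contradiction.

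Nor are the reasons for higher power empty. Other covariates, such as serostatus concordance, may explain variance. Data from before dropout can help in a repeated-measures model. Retention may exceed 85%. Only the baseline-outcome part of the first reason can be checked from the inputs, and it is small.

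**Conclusion.** The concern holds in a bounded form. For the 6-month contrast with 63 couples per arm and an intraclass correlation of 0.66, two-sided power for 12 points runs from about 34% at binomial variance to 56% at SD 0.35 and 69% at SD 0.30. It reaches 80% only at SD 0.264 or less, which the expected heaping makes implausible. For the average of the two follow-ups, power is about 53% at binomial variance and 80% at an SD of about 0.35 or less, which is possible but not documented. These results assume a two-sided test, a 12-point difference between arms, and the same autocorrelation of 0.15 between the two follow-ups. The SDs are assumptions. The expectation that actual power exceeds 80% is weakly supported as far as it rests on adjusting for the baseline outcome.

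**What to change.** In Power analysis, restate the power or the detectable difference for the actual primary contrast. Give the SD and its source, the sidedness and the number of follow-up visits, and use the intraclass correlation of 0.66 and autocorrelation of 0.15. Then choose one of two courses and make Data analysis agree with it:
- keep the 6-month contrast and state its lower power; or
- name the treatment effect averaged over the 3- and 6-month visits as primary, state its power for the SD adopted, and keep 6 months as a secondary contrast.

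The choice should be made without reference to outcome data by arm, since recruitment has begun. Limit the statement about higher actual power to what the inputs support. Reword the Limitations sentence so that it says what the trial is and is not powered for, in agreement with Power analysis.

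No extra couples or visits are needed. The cost is a less favourable stated power and, under the second course, giving up a purely 6-month primary claim.

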### Plans for dissemination

We hope that findings from this study will help reduce the impact of HIV on Latino male couples. We define dissemination as an ongoing, multi-directional process. Not only must these efforts be guided by science, but our approaches must be tailored to the intended audiences. Our anticipated audiences include (1) scientists, (2) prevention practitioners, (3) policy-makers, and (4) the community at-large. For the scientific community, we will use traditional dissemination vehicles, including manuscripts and presentations at international and national meetings. Given the study’s commitment to community and stakeholder involvement, we will work closely with our CAB and GALAEI to facilitate integration of findings into public health practice and the larger community.

Insights gathered from the first two CAB meetings have already served as the basis for an oral presentation at the 2017 American Public Health Association conference, focusing on the development of effective health communication strategies for recruiting and engaging Latino MSM. The aforementioned abstract details CAB members’ call for communication and recruitment materials that are culturally appropriate, are inclusive of in-group differences (including transgender individuals) and linguistic diversity, and avoid hypersexualized portrayals of Latino men, which several CAB members identified as a salient concern among current communication strategies targeting Latino MSM.

As the study progresses, we will elicit CAB members’ and agency staff and volunteers’ impressions of the study, ascertain their views on the pragmatic utility of the intervention, and generate ideas for further research and dissemination of findings. We plan to assist our local health department in planning initiatives and will explore other vehicles with our community partners to maximize utilization of our findings by local HIV prevention practitioners. Finally, we will present our findings to community-based organizations and their clients at seminars and workshops, and will work collaboratively to explore the relevance of the findings to their unique circumstances and settings.

## Discussion

The evidence indicating that HIV transmission often occurs within primary relationships [5, 6] suggests that focusing HIV risk reduction efforts on male couples may present a critical – albeit often overlooked – opportunity to reduce the spread of HIV among MSM. Moreover, the need for HIV prevention interventions to be culturally tailored and otherwise context sensitive is highlighted by a growing body of evidence supporting greater efficacy among such interventions [14]. The present study and related intervention make several advances in this area of HIV prevention, and build upon previous work in several innovative ways.

First, we focus on Latino MSM, an understudied and underserved group, disproportionately affected by HIV and AIDS and identified in the National HIV and AIDS Strategy as a group in need of targeted prevention efforts. Second, we are intervening at the level of the couple, where a high proportion of HIV transmission occurs. Intervening at this level offers a number of advantages over individual level interventions, and provides the opportunity to influence safer sex practices among two individuals simultaneously, to strengthen couple dynamics and relationship communication skills, in turn enhancing safer sex decision-making and negotiation skills, and to engage individuals who may not otherwise be targeted for individual-level prevention efforts, despite risk for HIV infection. These benefits have the potential to strengthen and enhance the broader public health impact of the intervention. Third, rather than developing an entirely ‘new’ intervention, we are refining an evidence-based HIV prevention intervention for black male couples to apply to Latino male couples. The resulting intervention, CLP, can thus advance more quickly through the testing process and be ready for widespread community implementation more rapidly. Fourth, we employ a novel outcome variable, conceptualizing ‘HIV protected acts’ to extend beyond condom use to include acts protected by PrEP and TasP.

### Limitations

Despite its unique advantages, there are several limitations. We will recruit a convenience sample, which limits generalizability. We acknowledge that the sample may not reflect the general population of Latino MSM. The budgetary constraints and the length of the project period of the MARI initiative limit our ability to include a 12-month follow-up. Thus, while we may detect change at 3 or 6 months post intervention, we will not be able to determine if the effects are sustained over time. Our sample size, although adequate to test for intervention effects, is not powered for efficacy. Thus, we cannot test the effects of moderators or mediators; moderation and mediation analysis are exploratory. Our primary outcome is limited to sexual activity with main partners. While appropriate for testing a couple-based intervention, we recognize that the HIV risk and protection with outside partners should also be considered. We will be conducting these as secondary analysis.

## Conclusion

Engagement of a CAB, rigorous measures testing, and systematic implementation processes are necessary prerequisites for the large-scale delivery of peer-led HIV interventions to improve HIV protection among Latino MSM. HIV prevention research trials that directly engage Latino MSM couples and key stakeholders are vital to inform culturally tailored interventions, improve HIV protection, and reduce HIV-related disparities that disproportionately affect Latino MSM. The present study not only advances HIV prevention research, but more importantly, if CLP results in significant behavior change, it holds promise in helping to reduce the HIV epidemic among Latino male couples.

## Trial status

We are currently recruiting study participants.

## Abbreviations

CAB: community advisory board
CLP: Connecting Latinos en Pareja
GEE: generalized estimating equations
MSM: men who have sex with men
PrEP: pre-exposure prophylaxis
QA: quality assurance
RCT: randomized controlled trial
SCT: social cognitive theory
STI: sexually transmitted infections
TasP: treatment as prevention
